### Sample size

Referring to previous studies of cognitive decline among patients with SCD [19–23], we assume that the MMSE score will decrease by 0.5 ± 0.5 points in the normal gait group and 0.7 ± 1.2 points in the abnormal gait group within 1 year; the ratio of abnormal gait to normal gait among outpatients with SCD is 1:2. Test efficiency 1-beta is set at 90%, while test level alpha is set at 0.05. An estimated 20% shedding rate, sample size of 1050 patients with a normal gait and 550 patients with an abnormal gait will be required. Therefore, a total of 1600 patients will be included.

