#### Neuropsychological evaluation

Participants will be evaluated on the following neuropsychological tests by trained doctors:Mini-Mental State Examination (MMSE), Chinese version translated by Mingyuan Zhang: evaluates time and place orientation, attention and calculation, recall, language, and copying. Scores range from 0 to 30 points, with a lower score indicating worse cognitive function.Montreal Cognitive Assessment (MoCA), Beijing version: evaluates visual-spatial ability, executive function, naming, memory, attention, language, abstraction, and orientation. Scores range from 0 to 30 points, with a lower score indicating worse cognitive function.The Stroop Color word test (CWT), Huashan version: evaluates semantic activation, dominant response inhibition, attention, working memory, and information processing speed. The time spent in each card and the number of errors will be recorded. A longer time cost or more errors indicate worse cognitive function.The digit span test (DST), a subtest of the Chinese version of the Wechsler Adult Intelligence Scale-Revised: evaluates immediate memory and attention. A shorter string of repeated numbers indicates worse cognitive function.

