### Outcomes

The primary outcome of this study will be the changes in the MMSE score in patients with SCD after 1-year follow-up.

The secondary outcomes of this study will be the changes in intelligent gait parameters (step length, gait speed, step frequency, step width, standing up time, and turning back time) and the changes in scores on other neuropsychological tests (MoCA, CWT, and DST) after 1-year follow-up, the prevalence of abnormal gait and cognition decline in patients with SCD, and the incidence of cerebrovascular events and falls in patients with SCD.

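### The 90% power assumes the smallest possible SD for MMSE change in the normal gait group, so it is a near best-case figure

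*Protocol article*

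**What the plan says.** The Outcomes section of the protocol article defines the endpoint: "The primary outcome of this study will be the changes in the MMSE score in patients with SCD after 1-year follow-up". Under Neuropsychological evaluation the MMSE is described thus: "Scores range from 0 to 30 points, with a lower score indicating worse cognitive function".

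The Sample size section refers to earlier studies of cognitive decline in this population and assumes that, within one year, the MMSE score will "decrease by 0.5 ± 0.5 points in the normal gait group and 0.7 ± 1.2 points in the abnormal gait group". It adds that "the ratio of abnormal gait to normal gait among outpatients with SCD is 1:2". On error rates it says: "Test efficiency 1-beta is set at 90%, while test level alpha is set at 0.05". The result is: "An estimated 20% shedding rate, sample size of 1050 patients with a normal gait and 550 patients with an abnormal gait will be required", a total of 1600. The section gives no reason why one group should have less than half the SD of the other on the same test over the same year.

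**The concern.** The normal-group SD of 0.5 is not merely low. For a whole-point score with a mean change of -0.5, it is the lowest value that is mathematically possible. It requires half of the normal-gait patients to score the same a year later and half to lose exactly one point. No one may gain a point and no one may lose two. That is hard to credit for two administrations a year apart across 14 hospitals. It also sits oddly beside the SD of 1.2 assumed for the abnormal gait group.

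The stake is how the result is read. The hypothesis is a greater decline with abnormal gait, and the planned difference is only 0.2 points. If the study finds no difference, the stated 90% power will bear on how strongly that finding counts against the gait marker. A figure taken from the edge of what is possible would make a null result look firmer than it is.

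**Working it through.** **Inputs.** From the Sample size section: mean changes -0.5 and -0.7 (difference 0.2), SDs 0.5 (normal) and 1.2 (abnormal), ratio 2:1, alpha 0.05, power 90%, loss 20%, group sizes 1050 and 550. Completers are 1050 × 0.8 = 840 and 550 × 0.8 = 440. Three readings are mine: the ± values are SDs, the test is two-sided, and the MMSE is scored in whole points. The scale implies the last but does not state it.

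**Step 1: reproduce the plan.** Comparison of two means with unequal variances:

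n(abnormal) = (1.960 + 1.2816)² × (1.2² + 0.5²/2) / 0.2² = 10.507 × 1.565 / 0.04 = 411.1, so 412; normal 2 × 411.1 = 822.2, so 823.

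Dividing by 0.8 gives 514 + 1028 = 1542. The stated 1600 is slightly higher, consistent with rounding up. A one-sided test would give 1257, and a common SD of 1.2 would give 2129. Neither fits, so the plan did use 0.5 and 1.2 as SDs in a two-sided calculation.

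**Step 2: the floor.** If the change X is an integer and its mean is -0.5, then |X + 0.5| ≥ 0.5 for every patient. So Var(X) ≥ 0.25 and SD ≥ 0.5, with equality only if X is 0 or -1 for everyone. A linear program over integer changes from -30 to 30 with mean -0.5 confirms a minimum of 0.500, with half the patients at 0 and half at -1.

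**Step 3: power with 840 and 440 completers.**

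SE = √(s_n²/840 + s_a²/440); power = Φ(0.2/SE − 1.96); difference detectable with 90% power = 3.2415 × SE.

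At the stated SDs: SE = √(0.000298 + 0.003273) = 0.0598; 0.2/0.0598 − 1.96 = 1.387; power 91.7%.

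| SD normal | SD abnormal | SE | Power for 0.2 | Detectable with 90% power |
|---|---|---|---|---|
| 0.5 (plan) | 1.2 (plan) | 0.0598 | 91.7% | 0.19 |
| 0.67 | 1.2 | 0.0617 | 90.0% | 0.20 |
| 0.8 | 1.2 | 0.0635 | 88.3% | 0.21 |
| 1.0 | 1.2 | 0.0668 | 84.9% | 0.22 |
| 1.2 | 1.2 | 0.0706 | 80.8% | 0.23 |

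Normal-group SDs other than 0.5 are assumptions. The last row applies the plan's own abnormal-group SD to both groups.

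**Step 4: how much slack there is.** For 90% power, s_n² may be at most 840 × [(0.2/3.2415)² − 1.44/440] = 840 × 0.000534 = 0.449, so s_n = 0.67. A patient who changes by +1 or -2 contributes 1.5² = 2.25 to the variance instead of 0.25, an excess of 2. With gains and losses balanced so that the mean stays at -0.5, the slack is used up when (0.449 − 0.25)/2, or about 10%, of normal-gait patients do so.

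**The case against.** A reader might infer that 90% power cannot be delivered. The documents do not support that. The floor is attainable in principle, the planned numbers give 91.7% power there, and 90% survives to a normal-group SD of 0.67. If no one were lost (1050 and 550 analysed), it would survive to about 1.12, although the plan itself expects 20% loss.

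Nor is there an arithmetic error, since the sample size follows from its inputs. Although the normal group is about two thirds of the cohort, at the stated SDs it supplies only about 8% of the variance of the difference (0.000298 of 0.003570). The SD of 1.2 in the smaller group drives the calculation, which limits the damage.

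A reader might also infer power as low as 62% or 40%. Those figures need SDs of 1.5 or 2.0 in both groups. They raise the abnormal-group SD above the stated 1.2, for which the document gives no basis and which the floor argument does not touch.

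The inputs are given to one decimal, so 0.5 could stand for a value up to 0.55. That would allow (0.3025 − 0.25)/2, or about 2.6%, of normal-gait patients to gain one point or lose two, which changes little. The cited studies are not available here, so whether they report 0.5 cannot be judged. That restrains any claim about where the value came from. It does not make a value at the floor a safe one for planning.

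**Conclusion.** The point holds as a weakness in a planning assumption. The normal-group SD sits at its theoretical minimum, and the stated 90% power is therefore close to the best the design could achieve. At a normal-group SD of 1.0 to 1.2, with the abnormal-group SD left at 1.2, power for 0.2 points is about 81% to 85%, a loss of 7 to 11 percentage points from 91.7%. At 1.2 in both groups, the chance of missing the planned difference is about 19%, nearly double the intended 10%. Larger SDs would lower power further, but they are not figures from the document.

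This rests on whole-point scoring, on reading ± as SD, on a two-sided test, on 20% loss and on a true difference of 0.2. It should be fixed. It does not invalidate the study or its sample size.

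**What to change.** Keep 1600 patients and revise the sample-size paragraph.

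- Justify the normal-group SD from data on MMSE change scores, or replace it with a value above the floor.
- Restate the power accordingly. For example, at an SD of 1.2 in both groups, 1280 completers give about 81% power for 0.2 points, or 90% power for about 0.23 points. The 0.23 describes what the design can detect and should not be presented as a new target effect.
- Add a short table of power and detectable difference over a range of SDs for each group, with undocumented values marked as assumptions.
- If the SD is checked on early 12-month data, estimate it separately by gait group. A pooled SD cannot settle the matter: with 840 and 440 completers, a pooled within-group SD of 1.2 fits 1.2 in both groups (81% power) and equally 0.5 and about 1.93 (about 57% power).

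The cost is some rewording, an optional SD check on data already being collected, and a less favourable stated power. No extra patients are needed. For scale, restoring 90% power for 0.2 points at SD 1.2 in both groups would take 710 + 1419 = 2129 patients.

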### Statistical analysis

All measurement data will be tested using the Shapiro-Wilk normality test. Normally distributed continuous measurement data will be expressed as mean and standard deviation, while non-normally distributed measurement data will be expressed as median and interquartile range. The t-test, Wilcoxon signed-ranks test, repeated measures t-test, or linear generalized model will be used to compare measurement data. The enumeration data will be expressed as a composition ratio or rate. The chi-square test or Fisher exact method will be used to compare enumeration data. Pearson linear correlation analysis or Spearman correlation analysis will be performed for correlation analysis. Survival will be estimated using a Kaplan-Meier survival curve. The propensity score matching method will be used to minimize the influence of other confounders. Subgroup analyses will include region and hospital levels. All cases with missing values will be deleted. A significant difference will be identified *P* < 0.05.

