SCD is an independent contributing factor to vascular cognitive impairment and dementia [8] that places a heavy burden on patients, their families, and society. The total payments in the US for people aged 65 and older with dementia were estimated to be $305 billion in 2020 and included long-term care and hospice services [9]. In China, the annual total cost associated with dementia was estimated to be $248.71 billion in 2020 [10]. The effective screening of SCD-related cognitive decline for preventing progression to dementia is challenging. Most neuropsychological scales are time-consuming, and their results are affected by language and education level. Gait is an indicator with advantages such as repetition and reliability. There is increasing evidence that a slow gait occurs in the early stages of dementia and may precede the decline on cognitive tests [11]. An acceleration in gait speed decline reportedly occurred 12.1 years before the onset of mild cognitive impairment [12]. There are many common causes of both cognitive decline and gait impairment, such as lesions in the cerebral cortex [13] (such as the prefrontal cortex), impaired executive function, cardiovascular diseases, and diabetes [14]. Motoric cognitive risk syndrome (MCR), a predementia syndrome, involves a slow gait and cognitive complaints and has the potential to be an alternative method for predicting the risk of cognitive decline in low- and middle-income countries [15]. A meta-analysis showed that the adjusted hazard ratio for MCR predicted the risk of developing incident cognitive impairment in individuals aged 60 years and older reached 2.0 (95% confidence interval [CI], 1.7–2.4) [11].

The current clinical gait assessment mostly depends on visual observations of clinical professionals, and its results are affected by large subjective factors. Professional gait analyzers, such as instrumented walkways and marker-based motion capture systems, are not used widespread in the clinical setting because of their high cost and low portability. Our team proposed a vision-based artificial intelligent gait analyzer for the rapid detection of gait spatiotemporal parameters and walking pattern classification based on videos of the Timed Up and Go Test (TUG) without the use of body markers [16]. By learning the gait diagnosis of three experts, the area under the curve of our intelligent gait analyzer for screening gait abnormalities was 0.96, with an accuracy of 90.14%.

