## Methods/design

### Study design

The ACCURATE-2 is a multicenter prospective cohort study that follows the changes in scores of neuropsychological test in patients with SCD to compare the differences between normal gait group and abnormal gait group, and analyzes the correlation between gait spatiotemporal parameters and the changes of neuropsychological test scores.

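### The gait-parameter correlations are planned without adjustment, and propensity score matching on gait group cannot supply it

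*Protocol article*

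**What the plan says.** The Background of the protocol article sets the primary objective as the relationship between gait features and cognitive change. The Study design section gives two parts: a comparison of the normal- and abnormal-gait groups, and an analysis that "analyzes the correlation between gait spatiotemporal parameters and the changes of neuropsychological test scores".

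For the second part, the Statistical analysis section states: "Pearson linear correlation analysis or Spearman correlation analysis will be performed for correlation analysis". It mentions no partial coefficient and no adjusted slope. On confounding it says: "The propensity score matching method will be used to minimize the influence of other confounders". It gives no matching ratio, caliper or covariate list. A linear generalized model appears among the options for comparing measurement data, without covariates and not in connection with the correlations.

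The Background lists causes common to gait and cognitive impairment, among them cardiovascular disease and diabetes. It also says of neuropsychological scales that "their results are affected by language and education level".

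The Sample size section powers an unmatched two-group comparison. It assumes that "the MMSE score will decrease by 0.5 ± 0.5 points in the normal gait group" and by "0.7 ± 1.2 points in the abnormal gait group within 1 year", and that "the ratio of abnormal gait to normal gait among outpatients with SCD is 1:2". Power is 90%, alpha 0.05 and dropout 20%, giving 1050 normal-gait and 550 abnormal-gait patients.

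**The concern.** A propensity score for abnormal versus normal gait balances covariates between those two groups. A Pearson or Spearman coefficient relates a continuous gait measure to MMSE change across patients, and within each group gait speed still varies with age, diabetes and heart disease. Running the correlation in the matched subset would not cure this, because matching breaks the link between the covariates and the label, not the link between the covariates and the continuous parameter.

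The plan as written can therefore report a significant correlation that reflects a shared cause. That bears on the article's stated goal of showing whether subtle gait abnormalities can act as a marker of cognitive decline: a gait measure that only stands in for age or comorbidity adds little to what the clinician already knows.

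A lesser question is whether matching weakens the group comparison, since the sample size makes no allowance for patients lost to it.

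**Working it through.** **1. The plan's sample size.** Two-sample comparison of means with unequal SDs, normal approximation, two-sided alpha 0.05 (sidedness is not stated; two-sided is the variant that fits), power 0.90, ratio 1:2, difference 0.7 - 0.5 = 0.2:

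- n(abnormal) = (1.2² + 0.5²/2) × (1.960 + 1.282)² / 0.2² = 412; n(normal) = 823.
- Divided by 0.8 for dropout: 515 + 1029 = 1544.
- Each group rounded up to the next 50: 550 + 1050 = 1600, as stated.

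Completers: 0.8 × 550 = 440, 0.8 × 1050 = 840, total 1280. SE = sqrt(1.2²/440 + 0.5²/840) = 0.0598, and power = Φ(0.2/0.0598 - 1.96) = 91.7%. The stated size is consistent with its inputs.

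**2. Size of a confounded correlation.** If a covariate is the only link between a gait parameter and MMSE change, the expected raw correlation is the product of its correlations with each. The inputs are assumptions, since the article gives no such figures. Age with gait speed is set at -0.4. Age with MMSE change (follow-up minus baseline) is varied from -0.1 to -0.3. The test is t = r × sqrt(1278)/sqrt(1 - r²).

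| Age with MMSE change | Spurious r | t | p |
|---|---|---|---|
| -0.1 | 0.04 | 1.43 | about 0.15 |
| -0.2 | 0.08 | 2.87 | about 0.004 |
| -0.3 | 0.12 | 4.32 | below 0.0001 |

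At n = 1280 any |r| above about 1.96/sqrt(1280) = 0.055 is significant at P < 0.05. With -0.4 for age and gait speed, an age correlation with MMSE change of about 0.055/0.4 = 0.14 in size is enough.

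**3. Power of the group comparison after matching.** The article states no ratio; 1:1 is assumed here, with no within-pair correlation. Power with m pairs = Φ(0.2/sqrt((0.5² + 1.2²)/m) - 1.96).

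| Abnormal-gait completers matched | m | Power |
|---|---|---|
| all | 440 | 89.7% |
| 90% | 396 | 86.5% |
| 80% | 352 | 82.3% |
| 70% | 308 | 77.0% |

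With all 440 matched, 840 - 440 = 400 normal-gait completers (47.6%) are dropped, yet the SE rises only from 0.0598 to 0.0620. The reason is that the abnormal-gait group supplies (1.2²/440)/0.0598² = 92% of the variance. What costs power is leaving abnormal-gait patients unmatched.

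**The case against.** The strongest reply is that the confirmatory hypothesis is the group comparison, for which a confounding method is named. The correlations appear neither among the outcomes nor in the sample size, and a raw association has some value for a marker. That limits the weight of the point but does not remove it: the correlations are a stated design aim, and the article fixes a method for them that leaves confounding in place. The size of the bias is also uncertain; at the low end of the assumed range the spurious r of 0.04 would not be significant.

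Several stronger readings are tempting, and the document does not support them.

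- *That matching is the sole route to adjustment.* It is the only method named for confounding, but the listed linear generalized model could carry covariates in the group comparison. The text does not say that it will.
- *That discarding about half of the normal-gait group undermines the power.* The 1:1 ratio is not in the article, matching details may sit in a fuller plan, and on the protocol's SDs the loss is about 2 points. Setting both SDs to 1.2 gives 70% matched power, but the unmatched comparison then already has only about 81%, so much of that fall is a separate criticism of the assumed SDs.
- *That the plan ignores differences between sites.* "Subgroup analyses will include region and hospital levels" plausibly refers to hospital tier, since the Setting section describes secondary and tertiary hospitals. A constant scoring offset at a site cancels in a change score. Any inflated type I error rests on assumed between-hospital variation.
- *That six parameters by four tests mean a 71% chance of a false positive.* That figure, 1 - 0.95²⁴, needs independent tests, and measures taken on the same patient are not independent.
- *That the Background names age or education as a shared cause.* It does not name age, and it ties education to test scores only.

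**Conclusion.** The point holds for the gait-parameter correlations. They are a stated aim, the stated coefficients are unadjusted, and matching on gait group cannot adjust them, while the Background itself lists causes common to both sides. This follows from the text and needs no numerical assumption. The illustrative size, r of 0.04 to 0.12 at 1280 completers, rests on assumed age correlations and on age being the only link.

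The power point is minor and conditional. Under 1:1 matching with the protocol's SDs and no within-pair correlation, power goes from 91.7% to 89.7% with full matching and to about 82% with 80% matched. A within-pair correlation of 0.1 would bring the full-matching figure back to 91.7%. It would be wrong to infer that the study is underpowered because of matching.

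The change should be made before analysis. It does not call the design or the sample size into question.

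**What to change.** - Replace the raw correlations as the basis for inference with a linear regression of MMSE change on each standardised gait parameter. Adjust for age, sex, education and vascular comorbidities, include hospital as a fixed or random effect, and use robust standard errors.
- Report adjusted slopes with confidence intervals, and apply Holm correction over the six parameters for MMSE. Pearson or Spearman coefficients can stay as description.
- Fit the same adjusted model for gait class on all patients, alongside the matched analysis, and report how many patients in each group were matched.
- Confirm that education is recorded. The Assessments section mentions demographic characteristics but does not name it.

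The cost is revised analysis wording, modest extra programming and a linearity check for age and education, for example with splines. No extra patients or visits are needed.

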### Grouping and follow-up plan design

During the baseline period, all participants will be evaluated by intelligent gait analyzer and neuropsychological tests. According to the intelligent gait report, each patient will be classified as normal gait group or abnormal gait group. All participants will be naturally observed for at least 1 year, and all their medical behaviors will be recorded. At six months after enrollment, all patients will be interviewed by telephone to collect falls events, cerebrovascular events, and the changes in medical behaviors during the follow-up period. The participants will be invited to undergo intelligent gait assessment and neuropsychological evaluation in the hospital at 12 months after enrollment, and falls events, cerebrovascular events, the changes in medical behaviors during the follow-up period will be collected. The details are presented in Fig. 1 and Table 1. All data will be encrypted and stored on the local server in Zhongshan hospital.

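### Deleting all cases with missing values leaves the 0.2-point MMSE comparison exposed to selective dropout, which the 20% allowance in the sample size does not cover

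*Protocol article*

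**What the plan says.** The Statistical analysis section of the protocol article states: "All cases with missing values will be deleted". The sentence is not limited to the variables of a given analysis and names no sensitivity analysis.

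The Sample size section allows for attrition ("An estimated 20% shedding rate") as a single figure, not split by gait group. It assumes that the "MMSE score will decrease by 0.5 ± 0.5 points in the normal gait group" and by "0.7 ± 1.2 points in the abnormal gait group within 1 year", so the difference sought is 0.7 − 0.5 = 0.2 points.

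MMSE is measured at baseline and at the 12-month hospital visit only (Grouping and follow-up plan design; Table 1). The contact in between is a call without cognitive testing: "At six months after enrollment, all patients will be interviewed by telephone to collect falls events, cerebrovascular events". For time-to-event data, the Statistical analysis section adds: "Survival will be estimated using a Kaplan-Meier survival curve".

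**The concern.** A patient who misses the 12-month visit has no MMSE change score and leaves the primary analysis. The completers' difference is then unbiased only if loss is unrelated to decline, or if its effects happen to cancel between the groups.

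There is reason to doubt that. Entry requires unaided walking and the ability to finish every test, and the 12-month visit asks for the same assessments in person. Patients who decline, fall or have a stroke may manage this less often. The study's own hypothesis puts more decline in the abnormal gait group. That group also has the wider assumed spread (SD 1.2 against 0.5), so the same dropout mechanism removes more of its worst decliners. Because the target is only 0.2 points, modest selection matters.

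Read literally, the rule has two further effects. A patient with both MMSE scores is dropped when some other item is missing, such as a Stroop card or the 1-year MRI. A patient with a 6-month event report but no 12-month visit is dropped, although a Kaplan-Meier analysis would count the event or censor at last contact.

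**Working it through.** **Inputs from the Sample size section.** Declines of 0.5 (SD 0.5) and 0.7 (SD 1.2); "the ratio of abnormal gait to normal gait among outpatients with SCD is 1:2"; 90% power; alpha 0.05 (taken as two-sided, since the article does not say); 20% loss; 1050 + 550 = 1600 enrolled.

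**1. The plan's own figure.** n(abnormal) = (1.2² + 0.5²/2) × ((1.96 + 1.2816)/0.2)² = 1.565 × 262.7 ≈ 411, and n(normal) ≈ 822. Dividing by 0.80 gives 514 + 1028 = 1542. The stated 1600 is a slight rounding up and not an error.

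**2. Loss of numbers alone.** With 20% loss, 440 abnormal and 840 normal remain. SE = √(1.44/440 + 0.25/840) = 0.0598, and power = Φ(0.2/0.0598 − 1.96) = 91.7%. If loss is unrelated to decline, power is still 90.0% at 25% loss, 87.9% at 30% and 82.6% at 40%. Precision is not the problem.

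**3. Selection.** Let p be the proportion lost in a group, and D the mean decline of its lost patients minus that of its retained patients. Then

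observed difference = 0.2 − (p_abn × D_abn − p_norm × D_norm).

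Two consequences follow:
- If p and D are the same in both groups, the bracket is zero and there is no bias.
- With 20% lost in each group, the difference vanishes when D_abn − D_norm = 0.2/0.20 = 1.0 point. Gaps of 0.25 and 0.5 points leave 0.15 and 0.10 (power about 71% and 39%).

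**4. A dropout model over a range.** Assume logit P(lost) = a + b × decline, with normally distributed decline, the same b in both groups, and a set to give the stated loss. In this model D is close to b × SD². For b = 0.1 that is 0.1 × 1.44 = 0.144 (abnormal) and 0.1 × 0.25 = 0.025 (normal). Numerical integration gives the values of D below. Power uses the SE of step 2 for equal loss. For 30%/15% loss it uses √(1.44/385 + 0.25/892.5) = 0.0634. Powers are good to about one percentage point.

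| Loss abnormal / normal | b | D_abn | D_norm | Observed difference | Power |
|---|---|---|---|---|---|
| 20% / 20% | 0.1 | 0.144 | 0.025 | 0.2 − 0.20 × 0.119 = 0.176 | 84% |
| 20% / 20% | 0.3 | 0.423 | 0.075 | 0.2 − 0.20 × 0.348 = 0.130 | 59% |
| 20% / 20% | 0.5 | 0.681 | 0.124 | 0.2 − 0.20 × 0.557 = 0.089 | 32% |
| 30% / 15% | 0.1 | 0.144 | 0.025 | 0.2 − (0.0432 − 0.0038) = 0.161 | 72% |
| 30% / 15% | 0.3 | 0.421 | 0.075 | 0.2 − (0.1263 − 0.0113) = 0.085 | 27% |
| 30% / 15% | 0.5 | 0.672 | 0.124 | 0.2 − (0.2016 − 0.0186) = 0.017 | 6% |

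The unequal split keeps overall loss near the planned figure: (0.30 × 550 + 0.15 × 1050)/1600 = 20.2%. The slopes and the split are assumptions, because the article gives neither.

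**5. Literal any-variable deletion.** As an illustration, suppose 2% is missing independently on each of 12 variables. Then 1 − 0.98¹² = 21.5% of completers are also lost, so 840/440 becomes about 659/345 and power falls to Φ(0.2/√(1.44/345 + 0.25/659) − 1.96) ≈ 84%. The 2% and the 12 are assumed.

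**The case against.** The strongest reply is that nothing in the article says who will drop out. The cohort starts mobile and testable, the expected mean decline is 0.5 to 0.7 points, and a fall of that size need not keep most patients from a visit. This stands, so the point has to be put conditionally and over a range of selection strengths.

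A reader might infer that deletion will wipe out the planned difference. The documents do not support that. Under the model above, near-erasure needs the strongest slope together with unequal loss. With equal loss it takes a gap of 1.0 point in excess decline between the groups. Weak selection costs little. If the excess were larger among normal-gait patients who are lost, the bias would run the other way.

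A reader might also infer that fall and cerebrovascular event rates will be biased downward. The article gives no basis for computing that, and the direction is not established.

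In a condensed article, the deletion sentence may mean exclusion analysis by analysis. On that reading the any-variable loss and the discarding of censored patients fall away, but the exposure of the primary outcome does not.

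Finally, imputation under missing-at-random would recover only part of the bias. With predictors assumed to explain 10%, 20% or 30% of the variation in decline, imputation within gait group moves the b = 0.5 estimate from 0.09 to about 0.10, 0.11 or 0.12 at equal loss, and from 0.02 to about 0.035, 0.05 or 0.07 at 30%/15%. This is correct and shapes the fix.

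**Conclusion.** The concern holds in conditional form. The article fixes an unqualified deletion rule, so this is not a detail left to an analysis plan that is not shown. The allowance for 20% loss protects power only against loss unrelated to decline.

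If greater decline makes return less likely, the complete-case difference falls from 0.20 to between about 0.18 and 0.09 at equal 20% loss, and to between about 0.16 and 0.02 at 30% abnormal against 15% normal. Power falls from 91.7% to between 84% and 32%, and to between 72% and 6%, respectively. These ranges rest on assumed dropout slopes from 0.1 to 0.5 per point, an assumed split, and the plan's means and SDs.

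In these scenarios the risk is a missed or understated association and not a false positive, and the study is observational. Should-fix is therefore the right grade.

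**What to change.** Replace the deletion sentence with the following:

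- Exclude a patient only from analyses whose own variables are missing.
- Censor time-to-event outcomes at last contact, keeping events reported at the 6-month call.
- Analyse MMSE change in all enrolled patients by multiple imputation within gait group (or inverse-probability weighting), using the baseline test scores, demographics, gait parameters, hospital, and the 6-month event and treatment data.
- Prespecify a delta-adjusted tipping-point analysis, with delta varied separately by gait group. This part addresses dropout that depends on the unobserved 12-month MMSE, which imputation under missing-at-random corrects only partly.
- Report attrition by gait group.
- Keep the complete-case result as a sensitivity analysis.

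The article already plans to collect this information, so the cost is extra programming. The conclusion may also have to be stated less firmly if the tipping point proves to lie within a plausible range.

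### The plan's own SDs and group split call for an unequal-variance test that the analysis section does not name; the equal-variance form could run at up to about 12% instead of 5%

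*Protocol article*

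**What the plan says.** The sample size section of the protocol article assumes that the MMSE score will "decrease by 0.5 ± 0.5 points in the normal gait group and 0.7 ± 1.2 points in the abnormal gait group", and that "the ratio of abnormal gait to normal gait among outpatients with SCD is 1:2". It adds that "test level alpha is set at 0.05", sets power at 90%, allows 20% loss, and arrives at 1050 normal-gait and 550 abnormal-gait patients, 1600 in all. It does not say whether the test is one- or two-sided, or which variance formula was used.

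The statistical analysis section states: "The t-test, Wilcoxon signed-ranks test, repeated measures t-test, or linear generalized model will be used to compare measurement data". It sets the threshold with "A significant difference will be identified" at P < 0.05. It does not say whether the t-test or the linear model assumes equal variances. It also announces propensity score matching, without a matching ratio and without saying whether the matched comparison is the primary one.

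**The concern.** The planned variances differ by a factor of 1.44/0.25 = 5.8, and the group with the larger variance is the smaller one. In that arrangement a pooled variance is dominated by the large, low-variance group. The standard error of the difference then comes out too small, the test rejects too often, and the confidence interval is too narrow. An ordinary linear model with one residual variance behaves in the same way. A larger sample does not cure this, because the inflation depends on the variance ratio and the allocation ratio and not on the total number.

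At stake is the primary comparison of one-year MMSE change between the gait groups. The assumed difference is only 0.2 points, so a standard error that is 20% too small bears directly on the conclusion. An analyst who takes the named tests in their classical form would meet this problem under the plan's own assumptions.

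**Working it through.** **Inputs, all from the sample size section.** SDs 0.5 (normal) and 1.2 (abnormal); difference 0.7 − 0.5 = 0.2; ratio 2:1; alpha 0.05, taken as two-sided; power 90%; loss 20%. Completers: 0.8 × 1050 = 840 and 0.8 × 550 = 440.

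**Step 1: the plan's own figure.** With separate variances and (1.960 + 1.282)² = 10.507:

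- n(abnormal) = (0.25/2 + 1.44) × 10.507 / 0.04 = 411.1.
- Total evaluable = 3 × 411.1 = 1233. Divided by 0.8, this is 1542. Rounding up within groups gives 824 + 412 = 1236, or 1545. Using the Welch t distribution gives about 1549.

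The stated 1600 is 3 to 4% above these, which is consistent with rounding up. At 840 and 440 completers the separate-variance power is 91.7%. Other two-sided routes, after allowing for loss, lie further away:

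| Variance used | Total |
|---|---|
| Separate variances | 1542 to 1549 |
| Weighted average, (2 × 0.25 + 1.44)/3 = 0.647 | about 956 |
| Simple average, (0.25 + 1.44)/2 = 0.845 | about 1249 |
| SD 1.2 in both groups | about 2129 |

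A one-sided separate-variance calculation gives 1260. So the two-sided separate-variance calculation fits best.

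**Step 2: true error of the equal-variance test at 840 and 440.**

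- Pooled variance = (839 × 0.25 + 439 × 1.44)/1278 = 0.659.
- Pooled SE = √[0.659 × (1/840 + 1/440)] = 0.0478.
- True SE = √(0.25/840 + 1.44/440) = 0.0598.
- Ratio = 0.0478/0.0598 = 0.799.
- True two-sided error = 2 × [1 − Φ(1.96 × 0.799)] = 2 × [1 − Φ(1.567)] = 11.7%, so a nominal 95% interval covers 88.3%.

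At an exact 2:1 split (853 and 427) the error is 12.3%. If the test were one-sided at 0.05, the error at 840 and 440 would be 9.4%. Simulation of 40,000 normal datasets at 840 and 440 gave 11.7% for the pooled test and 5.0% for Welch. Simulated whole-point data (4,000 datasets) gave 10.9% and 4.8%.

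**Step 3: sensitivity to the normal-group SD.** The abnormal-group SD is held at 1.2, with 840 and 440 completers:

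| Normal-group SD | Pooled SE | True SE | Ratio | True error |
|---|---|---|---|---|
| 0.5 | 0.0478 | 0.0598 | 0.799 | 11.7% |
| 0.8 | 0.0563 | 0.0635 | 0.886 | 8.2% |
| 1.0 | 0.0631 | 0.0668 | 0.945 | 6.4% |
| 1.2 | 0.0706 | 0.0706 | 1.000 | 5.0% |

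**Step 4: how realistic 0.5 is.** One patient's MMSE change is a whole number. A whole-number variable with mean 0.5 has variance of at least 0.5 × 0.5 = 0.25. The planned SD of 0.5 sits exactly on that floor: every normal-gait patient would have to lose either 0 or 1 point. Any improvement, or any loss of 2 points, pushes the SD up and the error down the table.

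**Step 5: matching.** With n patients in each group the pooled SE is √[(0.25 + 1.44)/2 × 2/n] = √(1.69/n). The separate-variance SE is √(0.25/n + 1.44/n), the same number. In a 1:1 matched sample the inflation from unequal spread therefore disappears.

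**The case against.** The strongest objection is that the plan never commits to a pooled test. A t-test may be Welch's, and the variance form is a detail commonly left to a full protocol or SAP, neither of which is shown. The only visible sign of intent, the sample size, points to unequal variances. This stands. A reader might infer that the primary test will run at 12%, or that the two sections contradict each other. The documents support neither inference, since both need the word pooled to be added to the text.

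Three further points also stand in part.

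- **Matching.** It could remove the problem if it is 1:1 and primary. The protocol article fixes neither, so the unmatched comparison remains possible.
- **Normality testing.** All measurement data go through Shapiro-Wilk, and whole-point MMSE changes may well fail it and lead to a rank test. The link from that result to the choice of test is implied only, and the calculation above does not cover rank tests.
- **The planning SD.** The 12% depends on a normal-group SD at its mathematical minimum. A more realistic reading is 6 to 8%.

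The objection does not remove the point. Under the plan's own SDs and split, the classical t-test and the constant-variance linear model do not hold the stated alpha, and a form that does is available at essentially no cost.

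**Conclusion.** The point holds as a conditional one, graded as a free improvement and not as an error that must be fixed. If the equal-variance form is used on the unmatched groups, two-sided, the true type I error lies between 5% and about 12%: the top under the planned SDs, about 8% at a normal-group SD of 0.8, and about 6% at 1.0. These figures assume about 840 and 440 completers, an abnormal-group SD of 1.2, and the same SDs holding when the true mean changes are equal. The sample size is not in question here, since 1600 is consistent with a separate-variance calculation.

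**What to change.** In the statistical analysis section, name Welch's t-test for unadjusted two-group comparisons of MMSE change. Name heteroscedasticity-robust standard errors (for example HC3) for linear models of MMSE change, with robust errors suited to the matching in matched samples. In the sample size section, state that the calculation used unequal variances.

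The cost is a sentence or two. Essentially nothing is lost if the variances prove equal, and under the planned SDs the separate-variance test still has 91.7% power at 840 and 440 completers, so the sample size need not change on this account.
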